## Abstract

**Background:**

Atrial fibrillation is a cardiac arrhythmia commonly encountered in a primary care setting. Current screening is limited to pulse palpation and ECG confirmation when an irregular pulse is found. Paroxysmal atrial fibrillation will, however, still be difficult to pick up. With the advent of smartphones, screening could be more cost-efficient by making use of simple applications, lowering the need for intensive screening to discover (paroxysmal) atrial fibrillation.

**Methods/design:**

This cluster randomized trial will examine the effect of using a smartphone-based application such as FibriCheck® on the detection rate of atrial fibrillation in a Flemish general practice population. This study will be conducted in 22 primary care practices across the Flanders region of Belgium and will last 12 months. Patients above 65 years of age will be divided in control and intervention groups on the practice level. The control group will be subjected to standard opportunistic screening only, while the intervention group will be prescribed the FibriCheck® app on top of this opportunistic screening. The difference in detection rate between control and intervention groups will be calculated at the end of the study.

We will use the online platform INTEGO for pseudonymized data collection and analysis, and risk calculation.

**Discussion:**

Smartphone applications might offer a way to cost-effectively screen for (paroxysmal) atrial fibrillation in a primary care setting. This could open the door for the update of future screening guidelines.

**Trial registration:**

ClinicalTrials.gov NCT04545723. Registered on September 10, 2020.

## Administrative information

The order of the items has been modified to group similar items (see http://www.equator-network.org/reporting-guidelines/spirit-2013-statement-defining-standard-protocol-items-for-clinical-trials/).

## Introduction

### Background and rationale {6a}

#### Incidence and prevalence of atrial fibrillation

Atrial fibrillation (AF) is one of the most common cardiac arrhythmias. Consequently, it is also frequently encountered in primary care. According to the INTEGO database (containing routinely collected general practice data of over 400,000 patients in Flanders [1]), the incidence of AF in a Flemish general practice population was 3.2 per 1000 patients in 2020 [2]. Estimates around the globe vary widely depending on the source. Current prevalence estimates range from 1 to 4% for Western countries [3], with a generally rising prevalence [4–6].

AF carries a significantly elevated risk of stroke. Relative risk of stroke in patients with AF varies between 2.6 and 4.5 for patients over 60 years old, compared to patients without AF [7]. The high morbidity and mortality of stroke is evident, and it is often the first presentation of silent AF [8]. It therefore seems useful to invest in screening strategies to identify those patients who have a higher risk of AF and need more intense monitoring, which may reduce healthcare costs brought about by hospitalizations for stroke [9, 10]. Furthermore, because some patients with AF will present with infrequent episodes—so-called paroxysmal atrial fibrillation (PAF)—the need for effective screening measures becomes clear [11]. For example, in a Portuguese population aged 40 and older, who were referred for 24-h continuous Holter monitoring, the prevalence of PAF was 2.5%, compared to 9.4% for persistent AF [12].

Still, many patients go undiagnosed. A recent study in the USA put the proportion of “silent” AF at 2.4% of the adult population [13].

#### Screening

Stroke risk in AF is commonly calculated using the CHA_2_DS_2_-VASc score (congestive heart failure, hypertension, age, diabetes, stroke, vascular disease, sex) [14]. Originally devised as a tool to predict the risk of stroke in AF, it may be less applicable to AF risk prediction in general [14]. Various other scoring systems have been developed over the years, and more recently the CHARGE-AF score has come to the foreground. For this score, data from three large cohorts in the US was used to predict AF risk in primary care settings [15].

The CHARGE-AF score is sufficiently validated to be used in AF stroke risk prediction and seems to perform better than the CHA_2_DS_2_-VASc score [16]. Furthermore, the CHARGE-AF score uses variables that are readily available from patient files in a primary care setting [15]. The variables of the (simple) CHARGE-AF score include age, race, height, weight, systolic and diastolic blood pressure, smoking status, antihypertensive medication use, diabetes, heart failure, and myocardial infarction [15].

Opinions on the best approach to screening for AF in general practice are not unanimous. There are various ways to go about it: pulse palpation, which, when revealing an irregular pulse, can lead to a clinical diagnosis of AF, or by performing an electrocardiogram (ECG) to confirm AF after palpation of an irregular pulse. These methods could be used in either specific at-risk populations, or generally in every patient above a certain age, a risk category on its own. Both methods are available in a primary care setting, but performing an ECG is especially time-consuming. The most cost-effective strategy at this moment is likely to involve opportunistically screening every patient 65 years and older by pulse palpation or heart auscultation [17], taking an ECG only in those who have an irregular pulse [18]. However, a systematic full screening of older patients is not cost-efficient [18, 19].

Patients who present with persistent AF are unlikely to be missed using the strategy outlined above. However, patients with the paroxysmal variant might still slip through and never be picked up using these methods. Holter registrations or even longer-term event recorders (in symptomatic patients) could partially solve this issue, but neither is very practical in general usage and their interpretation is very time-consuming.

#### Other options for screening

In recent years, various devices have been marketed as workarounds to solve the issue of detecting PAF in the general population. In addition, most offer a very user-friendly and easily accessible interface. Examples are heart rate and blood pressure monitors [20], one-lead ECG devices or smartphone apps [21, 22], or event recorder patches [23].

The global advent of smartphones might offer a unique opportunity to mediate the problem of detecting PAF [22, 24]. Apps carry the extra advantage of not needing additional hardware. The FibriCheck® app (Qompium, Hasselt, Belgium) has recently been developed to aid in the detection of PAF. It is based on the photoplethysmography technique, using only the phone’s built-in camera and flash [25]. The app has been shown to accurately detect AF in a primary care setting [26], with an estimated sensitivity and specificity of 95.6% and 96.6%, respectively. An ECG will still be necessary for diagnosis, but there will be less need for continuous ECG or event recording and the data can be easily visualized and interpreted by a general practitioner or cardiologist.

A recent pilot study by our team, to assess the ease-of-use and implementation of the FibriCheck® app in primary care, found high rates of patient satisfaction and compliance [27].

#### Aim of the study

Implementing the FibriCheck® app in a primary care setting could solve the problem of screening for AF and, specifically, detecting PAF. Therefore, the aim of this study is to investigate the effect of a case-finding strategy with the FibriCheck® application on the detection rate of AF in comparison with opportunistic screening (i.e. pulse palpation, followed by an ECG) in patients with a high risk of AF in general practice.

### Objectives {7}

The primary objective of this study will be to investigate the effect of a case-finding strategy with the FibriCheck® smartphone application on the detection rate of AF in comparison with opportunistic screening (i.e., pulse palpation, followed by an ECG) in patients with a high risk of AF in general practice. The secondary objective is to keep track of thrombo-embolic complications, death, and compliance with measurements.

### Trial design {8}

This study will be a cluster randomized trial: primary care practices will be randomized and divided into a control and intervention group. Allocation of control and intervention groups will be done by simple balanced randomization (1:1).

## Methods: Participants, interventions, and outcomes

### Study setting {9}

This study will take place in the eligible Flemish primary care practices in the INTEGO network.

The INTEGO network is a morbidity registry containing coded contents of the electronic health records of some 400,000 patients from 100 general practitioner’s offices all over Flanders. The information is automatically collected during daily practice and contains diagnoses, year of birth, gender, prescriptions, lab results, and various biomedical parameters such as blood pressure, height, weight, etc. [1]. The INTEGO procedures have been validated by the Belgian Privacy Commission. The registry is hosted on the Healthdata platform (www.healthdata.be) [28].

Patients coming to the eligible practices, as well as the practices themselves, will be recruited separately. They will fill in separate consent forms. After consent is given by the patient, the GPs of the recruited practices will explain the study outline and specific details, such as the installation and use of the app, at the first consultation, after which the study period for that specific patient will commence. General care will proceed as normal.

### Eligibility criteria {10}

To be eligible for inclusion in the study, *practices* must conform to the following conditions:
It is a Flemish primary care practice in the INTEGO network.The practice uses an electronic health record (EHR), automatically linked to the INTEGO database.ECG devices used for diagnosis (i.e., confirmation of AF) must be 12-lead.The physician signs a specific study consent form.

To be eligible for inclusion in the control or intervention groups of the study, *patients* must conform to the following conditions:
The patient is 65 years or older.The patient has an electronic medical record (EMR) in the practice. This EMR contains all the patient information, for instance regarding medical history and medication, and is managed by the general practitioner.If the patient will be prescribed the FibriCheck® app, he/she signs the relevant patient consent form. Patients in the control group will also be required to sign a consent form.

Exclusion criteria for both the control and intervention group will be defined as follows:
The patient has already been diagnosed with AF.The patient is already under anticoagulant therapy.The patient has a pacemaker. Active pacing during measurements influences the results obtained with the FibriCheck® app [26].The patient is unable to use the FibriCheck® application independently due to cognitive disorders, functional limitations, visual impairments… These will be identified using diagnosis codes in the patient file.

Drop-out criteria for patients in the intervention group will be defined as follows:
Less than 20 measurements with the FibriCheck® app during the study period.Less than 2 measurements per day during the study period.On patient request, for whatever reason.

### Who will take informed consent? {26a}

We will use two different consent forms in this study; practices will be given a study leaflet by the study personnel, outlining the study procedure and required data, together with their own consent form. They will be given one week to decide whether they want to participate. Patients in both arms of the study who want to be included will be given a study leaflet and a separate consent form, in this case by the participating physician. They will also be given one week to decide. They can make an appointment with their GP to hand in the signed consent form during this period. Patients who are not heard from will be contacted by email or phone to ask whether they still want to be included in the study and if so, to provide a signed consent form.

### Additional consent provisions for collection and use of participant data and biological specimens {26b}

Not applicable for this type of study, no biological specimens will be collected.

## Interventions

### Explanation for the choice of comparators {6b}

The most cost-effective strategy for AF screening at this moment is likely to involve opportunistically screening every patient 65 years and older by pulse palpation or heart auscultation [17], taking an ECG only in those who have an irregular pulse [18]. Systematic full screening of older patients is not cost-efficient [18, 19].

### Intervention description {11a}

In every cluster designated as an intervention group, patients aged 65 or older will be selected according to the criteria outlined above. Within this group, high-risk patients will be identified using the CHARGE-AF score and will be prescribed the FibriCheck® app. An integrated tool in the medical software package will calculate this score from the available parameters in the EHR. If needed, physicians will be asked to input missing data at the first consultation. Data for this score will be automatically extracted from the EHR from INTEGO. All high-risk patients will thus be flagged as such on the INTEGO platform. Physicians will also need to inform and educate patients about their high-risk status, as we consider this good clinical practice.

These high-risk patients will subsequently be informed about the study and possible enrolment and be given a study information letter describing the study procedure and purpose in detail.

Interested patients will be prescribed the FibriCheck® application after informed consent is given. Patients not in possession of a smartphone will be supplied one for the duration of the study. The application needs to be downloaded and patients will be asked to create a numbered account (in the format “patient00x,” etc.) and supply general details such as age and gender. A specific QR code links the patient’s account to the physician’s dashboard, so the latter can easily follow up.

The study will be conducted over the course of 12 months in general practices in the Flanders region of Belgium. Patients will be followed for a total of 4 weeks. Measurements and other data will be collected and interpreted at the end of this period. Positive measurements will be given immediate attention. A minimum of 20 measurements in total per patient in the intervention group is necessary to be considered for inclusion in the study.

To be able to track patients in the intervention group who were prescribed the FibriCheck® app, physicians will be asked to flag the specific patient file with a note saying “FC” or “FibriCheck,” or using the specific and personal ID created on the FibriCheck® app to link the app data to the patient file.

Every participant will be asked to measure at least twice a day (in the morning and in the evening) and if there are complaints such as dizziness or palpitations. After the measurement, the patient will be asked for his activities up to the measurement and certain symptoms. Participants are never asked to self-palpate their pulse, this will only take place at the GP’s office.

Measurements are available for the treating physician and a cardiologist, who will interpret the results within 24 h. Additionally, an electronic notification will be sent immediately to the interpreting physicians in case of an abnormal result. Physicians will be asked to review these results at least once every 24 h. At the end of every participant’s study period, a summarizing report will be sent to the treating physician.

When a positive result (red) has been found (indicating the possibility of AF), the patient will be contacted within 48 h for a formal 12-lead ECG. Patients themselves will also be instructed by the app to contact their GP for follow-up in case a possible AF has been found. If this ECG is inconclusive, a 2-week Holter measurement will be ordered. If AF is confirmed, rate or rhythm control and anticoagulant therapy will be started, or the patient will be referred to a cardiologist for further workup. The CHA_2_DS_2_-VASc score will be used to calculate the risk of thrombosis, and together with the HAS-BLED score [29], indicating the risk of bleeding, it will guide anticoagulant therapy [30].

If a positive FibriCheck® screening cannot be confirmed with 12-lead ECG or 2-week Holter, the patient files will be marked with a special code in the EHR and flagged for future, more intensive screening (with both the application and an ECG at consultation).

In addition to screening with the app, patients in the intervention group will also receive standard opportunistic screening: pulse palpation and a 12-lead ECG when an irregular rhythm is found.

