### Outcomes {12}

#### Primary outcome measures

##### Detection rate of AF in patients 65 years and older

The detection rate of AF in both the control and intervention group will be calculated after 4 weeks. A significant difference in both groups will be noted. Compared with previous studies of similar design [32–34], we will realistically assume a 2-fold increase in the detection rate of AF in the intervention group to be significant.

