##### Average time to detection of AF

We will compare the average time from the beginning of the study to the primary endpoint, the diagnosis of AF, in both study arms.

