### Participant timeline {13}

The study will be conducted over the course of 12 months in general practices in the Flanders region of Belgium, planned to run from January 2022 to December 2022.

Allocation of control and intervention practices is planned to start around November 2021. Eligible participants will be followed in their usual primary care practice, and are recruited by the participating physician when they visit for whatever reason. They will be provided an information leaflet, a consent form, and 1 week decision time.

Participants will be followed for a total of 4 weeks. Measurements and other data will be collected and interpreted at the end of this period. After the total study period of 12 months, the resulting data will be analyzed.

A schematic overview of the timeline can be found in Table 1. A visual representation of the study flow can be found in Fig. 1.

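### The four-week outcome cut-off does not fit the confirmation pathway: a red result after about day 12 that needs a full Holter may be unresolved at day 28, and no rule says whether it counts

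*Protocol article*

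**What the plan says.** **The cut-off.** The primary outcome text under Outcomes {12} states: "The detection rate of AF in both the control and intervention group will be calculated after 4 weeks". Intervention description {11a} gives the same horizon for follow-up: "Patients will be followed for a total of 4 weeks. Measurements and other data will be collected and interpreted at the end of this period". Participant timeline {13} repeats it and adds when the trial as a whole is analysed: "After the total study period of 12 months, the resulting data will be analyzed".

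**What counts as a case.** The second outcome listed as primary names the event: "We will compare the average time from the beginning of the study to the primary endpoint, the diagnosis of AF, in both study arms". A red app result does not meet that definition, because the Introduction says of the app: "An ECG will still be necessary for diagnosis".

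**How a red result becomes a diagnosis.** Under Intervention description {11a}, "the patient will be contacted within 48 h for a formal 12-lead ECG", and "If this ECG is inconclusive, a 2-week Holter measurement will be ordered". The same section treats a red result as unconfirmed only once the ECG or Holter has failed to confirm it.

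**The comparator.** Opportunistic screening is described in both arms as pulse palpation followed by an ECG when the rhythm is irregular. No Holter stage and no time limit are given for it.

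**The concern.** Patients measure up to the last day of the four weeks, and the outcome is read at the end of the same four weeks. A patient whose app turns red on day 20 and whose ECG is inconclusive can still be wearing the Holter on day 28. At that point the patient is neither a confirmed case nor, by the protocol's own pathway, an unconfirmed one.

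The mismatch is unlikely to be neutral between arms. The two-step confirmation with a long recording is written for app results. It matters most for paroxysmal AF, where an ECG taken a day or two after the episode is most likely to miss it, and paroxysmal AF is what the app is meant to find. If such patients are scored as not detected, the app arm loses true cases triggered inside its own screening period and the difference shrinks.

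Time to detection has the same problem. A case dated by the red result and one dated by its confirmation can differ by 16 days or more, and the protocol does not say which date applies.

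The trial is unblinded, so a rule left open here could be settled after results by arm are known.

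**Working it through.** The protocol states no last day on which a red result can still be confirmed, so there is no figure of its own to reproduce. The check sets the stated durations against each other.

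**Inputs**

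- Outcome reading and end of follow-up: 4 weeks = 28 days (Outcomes {12}; Intervention description {11a}; Participant timeline {13}).
- Red result to contact for ECG: up to 48 h = 2 days (Intervention description {11a}). This limits contact, not performance of the ECG.
- Holter after an inconclusive ECG: 2 weeks = 14 days (same section). No limit is given for fitting or reading.

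**Step 1. Last day on which a full Holter can finish by day 28**

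Last day = 28 − (days to ECG and fitting) − 14.

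- Full 48 h used, ECG and Holter following at once: 28 − 2 − 14 = day 12.
- ECG and Holter both started on the day of the red result: 28 − 0 − 14 = day 14.
- One further day of waiting beyond the 48 h: 28 − 3 − 14 = day 11.

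Day 14 is therefore the best case, day 12 follows from the stated limits, and any wait for ECG, fitting or reading makes it earlier.

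**Step 2. Share of the screening period after that day**

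- After day 12: (28 − 12)/28 = 16/28 = 57%.
- After day 14: 14/28 = 50%.
- After day 11: 17/28 = 61%.

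**Step 3. What this implies for cases**

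Let *h* be the share of app-triggered cases that need a full Holter. If red results are spread evenly over 28 days, the 48 h is the only wait, and every Holter case after day 12 is missed, the share of app-triggered cases missed is *h* × 16/28. The protocol gives no value for *h*. With assumed values:

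- *h* = 0.10: 0.10 × 0.571 = 6%.
- *h* = 0.25: 0.25 × 0.571 = 14%.
- *h* = 0.50: 0.50 × 0.571 = 29%.

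These are ceilings for each assumed *h* under the stated conditions, not estimates. A Holter that shows AF before its fourteenth day lowers them. Red results confirmed on the first ECG are affected only if they occur in the last days of the window.

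**Step 4. Earliest cut-off that fits the pathway**

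Red result on day 28, full 48 h, full Holter: 28 + 2 + 14 = day 44. Any further wait needs a later date; day 56 leaves 56 − 44 = 12 days for ECG, fitting, reading and coding.

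**The case against.** **No exclusion is stated.** A reader might infer that red results after day 12 that go to Holter cannot count. The text does not say that. It says when the rate is calculated, not that a diagnosis must be dated by day 28. Analysis follows the full 12 months, the data come from health-record extraction in which later diagnoses could still appear, and the sample size section expresses the outcome per year. This stands: the defect is a cut-off and a pathway that do not fit, with no rule to reconcile them. It does not remove the point, because none of those passages supplies a run-out period, and the outcome definition itself says four weeks.

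**Case dating belongs in an analysis plan.** Usually so, and a bare omission would not be worth raising in a condensed article. Here the article states both the cut-off and the pathway, and the two conflict on the page.

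**Only the app arm is affected.** This is another tempting inference. No time limit is set for the control ECG, nothing is said about an inconclusive one, and usual care continues, so control work-up may also run past day 28. What is supported is that the effect falls mainly on the app arm.

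**Even timing is doubtful.** The Discussion cites a yield of 0.4% from a single measurement against 1.4% over a week, so 0.4/1.4 = 29% of that week's yield came at the first reading. Early findings may be largely persistent AF that the ECG confirms, so this does not settle when Holter-dependent cases arise. It does show that even timing cannot be presumed, and no percentage of lost cases should be quoted as an estimate.

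**Conclusion.** The point holds as a mismatch between two things the protocol states. Under a literal four-week cut-off, a red result after about day 12 (day 14 at best, earlier with any wait) that needs a full Holter may not be a confirmed diagnosis when the outcome is read. The consequence would be an undercount mainly of paroxysmal AF in the app arm, biasing the comparison toward no difference, and an ambiguous time to detection.

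The size cannot be derived from the documents. The firm part is that 16 of 28 screening days lie after day 12. The 57% ceiling on the Holter-dependent share assumes even timing and no wait beyond the 48 h; how large that share is remains unknown. The arithmetic is secure, and the direction of bias is well supported provided the literal cut-off is what is applied. The documents do not show that such cases are excluded, or that control patients are untouched.

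It should be corrected before the outcome data are extracted.

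**What to change.** Leave the four-week app period and the confirmation pathway as they are, and change only the outcome definition under Outcomes {12}:

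- Count AF confirmed by 12-lead ECG or Holter and coded in the health record by one fixed day after the patient's start, the same in both arms. The day must be at least 44; day 56 is one workable choice.
- State that in the app arm this includes confirmations of red results from days 0–28.
- Apply the same ascertainment window to control patients without requiring a dated palpation finding, since the description of INTEGO data under Study setting {9} does not list one.
- State whether time to detection uses the trigger date or the confirmation date. Because control patients may have no recorded trigger date, the confirmation date is the one more likely to be available in both arms.

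**Cost.** No added procedure or visit. With day 56, extraction for the last patients moves 56 − 28 = 28 days later. Some AF unrelated to the four-week screening will be counted in both arms: if the protocol's baseline of 13.65 per 1000 per year applied, about 13.65 × 28/365 = 1.0 per 1000 for days 29–56, or 13.65 × 16/365 = 0.6 per 1000 if the date is day 44. If equal in both arms, these leave the expected absolute difference unchanged but dilute a ratio. That is a reason to set the date no later than practical delays require, and to fix it before results by arm are seen.
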